#### Preparatory Phase

Participants will undergo a robust screening interview to ensure understanding and absence of contraindications for MRI scanning. Before the task phase fMRI, participants will be thoroughly informed and trained. Communication with the operator will be maintained throughout the scan. Incidental findings requiring medical intervention will be disclosed, and participant comfort will be ensured during scanning. All scans will be reviewed by a qualified radiologist, and any clinically significant incidental findings will be communicated confidentially to the participant along with appropriate referral advice for further evaluation and management as per institutional protocols. Verbal communication will be limited due to MRI noise, and the participants will use a 4-button fiber-optic response box positioned for use with their right hand to communicate and record behavioral responses during tasks. To mitigate the effects of scanner noise, participants will wear earplugs. Head motion will be minimized using foam pads and a headband to ensure stable positioning throughout the MRI scans. Metallic items will be removed, and participants will wear MRI-compatible attire. Participants in both the trial and control groups will be directed to avoid heavy meals within 2 hours before and 1 hour after *nasya karma*. Both groups will refrain from consuming coffee, tea, or caffeinated drinks for 12 hours preceding the fMRI. In contrast, the control group will undergo resting state mapping on both the 1st and 14th days, whereas the participants in the intervention group will undergo the *nasya karma* procedure lasting approximately 30 to 45 minutes, after which participants will proceed to the MRI room. Participants in the control group will proceed directly to the MRI without any intervention.

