**Methods:**

A total of 60 healthy volunteers in the age group of 20 to 40 years who fulfill the selection criteria will be recruited for this randomized controlled trial at the National Ayurveda Institute for Panchakarma, Cheruthuruthy, Kerala, India, and randomized in a 1:1 ratio to either the intervention group (n=30; group 1, receiving *nasya karma* with *anu taila*, an oil-based formulation manufactured using a paste and decoction of herbal medicines with oils as the base material, for a period of 14 days) or the control group (n=30; group 2, not receiving any intervention). The participants will undergo task-based and resting fMRI on day 1 (twice on day 1 before administration and 15 minutes after *nasya karma* for participants in group 1) and day 14 to map the neurophysiological response to *nasya karma* of the brain. A comprehensive neuroimaging protocol using structural magnetic resonance imaging and fMRI will be used in the study. The effect of *nasya karma* on sleep, psychological well-being, cognition, and quality of life will be assessed on the 1st and 30th days in both groups.

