### Eligibility Criteria

Apparently healthy volunteers aged 20 to 40 years who are physically independent, ambulatory, and right-handed; have a BMI of 18.5 to 24.9 kg/m^2^; and are willing to participate and provide written informed consent will be included in the study. Only those who agree to abstain from beverages such as coffee, tea, energy drinks, or other stimulants beginning 12 hours before undergoing fMRI will be considered for recruitment. The healthy status of volunteers will be confirmed through the absence of any active or chronic disease, as determined through a comprehensive medical evaluation that will include a detailed medical history, complete physical examination (including vital signs), 12-lead electrocardiogram, hematology, blood chemistry, serology, psychological assessment, and urinalysis, among other tests.

Individuals with any disease or symptom, with a history of psychiatric disorders as assessed using the Mini-International Neuropsychiatric Interview, with psychosomatic disorders, who used psychotropic medications known to interfere with the dopaminergic system or sedatives within the previous 6 months, with a family history of psychiatric diseases, with past or current abuse of psychoactive drugs, or who use alcohol or smoke will be excluded. Individuals contraindicated for magnetic resonance imaging (MRI), such as those with medical implants, retained wires (eg, temporary pacing), an increased risk of myocardial infarction or other cardiac problems, known pregnancy, nausea (due to aspiration risk), metallic dental work, cochlear implants, body jewelry, and other metallic foreign objects implanted in the body will not be eligible either. Individuals with cognitive impairment, women in the menstrual phase, those with intracranial abnormalities that could adversely affect the interpretation of brain scans, and those who self-identify as claustrophobic are also not eligible for participation in the study. In addition to this, participants deemed unfit for *nasya karma* therapy [10], such as those with fever, rhinitis, cough, or other inflammatory conditions as indicated in the Ayurveda treatises, will be excluded.

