### Secondary Outcome Measures

These include the therapeutic effects of *marsha nasya karma* on cognitive function assessed via the Montreal Cognitive Assessment scale [11], perceived stress assessed using the Perceived Stress Scale [12], anxiety assessed using the Hamilton Anxiety Rating Scale [13], and health-related quality of life assessed using the 36-Item Short Form Health Survey [14]. The secondary outcomes will be assessed before the intervention and on the 1st and 30th days following the *nasya karma* therapy.

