#### Statistical Analysis

##### Overview

The modified intention-to-treat principle will guide the analysis for all outcomes within the full analysis set. Quantitative data will be summarized using mean, SD, minimum, maximum, and median values. Enumeration data will be presented as frequency and the corresponding percentage. Intragroup comparisons will be conducted using the Student paired *t* test or Wilcoxon signed rank test for continuous variables and the chi-square test for categorical variables. Intergroup comparisons will be conducted using the independent-sample *t* test or the Mann-Whitney *U* test. Significance thresholds will be set at *P*<.05 for all 2-tailed tests.

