**Clinical assessment**							
	Group A						✓
	Group B						✓

^a^fMRI: functional magnetic resonance imaging.

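### On the abstract's schedule, baseline scales fall on a caffeine-free scan day and day-30 scales do not, so within-group paired tests cannot separate a nasya effect from changed test conditions

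*Protocol article*

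**What the plan says.** **Caffeine rule.** The Preparatory Phase section states: "Both groups will refrain from consuming coffee, tea, or caffeinated drinks for 12 hours preceding the fMRI". Under Eligibility Criteria, only volunteers who agree to avoid coffee, tea, energy drinks and other stimulants "beginning 12 hours before undergoing fMRI will be considered for recruitment". Both statements attach the rule to the scan. Habitual caffeine use is not an exclusion.

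**Scan days.** The abstract says "The participants will undergo task-based and resting fMRI on day 1" and again on day 14. The Preparatory Phase section says "the control group will undergo resting state mapping on both the 1st and 14th days". Table 1 shows the same two days for both groups and no scan on day 30.

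**Scale days.** There are three accounts.
- Abstract, Methods: sleep, psychological well-being, "cognition, and quality of life will be assessed on the 1st and 30th days in both groups".
- Secondary Outcome Measures: "The secondary outcomes will be assessed before the intervention and on the 1st and 30th days following the" therapy. The first of these assessments has no date.
- Table 1: the "Clinical assessment" rows carry ticks under day 30 only, for both groups, as far as the extracted table can be trusted.

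**Tests.** Statistical Analysis, Overview: "Intragroup comparisons will be conducted using the Student paired" *t* test or the Wilcoxon signed rank test. Between-group comparisons use the independent-sample *t* test or Mann-Whitney *U* test. The threshold is .05, two-tailed, for all of them.

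**The concern.** A before-after test on a scale is informative only if the scale is given under like conditions both times. On the abstract's schedule it is not. The first assessment shares a day with an MRI session and a 12-hour stimulant restriction. The last has neither a scan nor any condition that the article states. If those circumstances move anxiety, stress or cognition scores at all, the change from day 1 to day 30 contains that movement, and the paired test in the nasya group cannot remove it.

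This matters because the paired tests are planned at the same significance threshold as the between-group tests, the Secondary Outcome Measures section presents the scales as showing therapeutic effects, and the Interventions section describes comparison with baseline. A significant paired result in the nasya group could therefore be reported as an effect of treatment when it reflects only the setting in which the scale was completed.

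**Working it through.** **Step 1. Which scale visits share a condition?** The plan has no figure of its own to reproduce here, so the first check is to set the schedule readings side by side. Sessions on alternate days over 14 days, 7 in all, fall on days 1, 3, 5, 7, 9, 11 and 13, so the first day after therapy is day 14, a scan day.

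| Reading | Baseline scales | Later scales | Like conditions? |
|---|---|---|---|
| Abstract | Day 1, scan, abstinence | Day 30, no scan, condition not stated | Not ensured |
| Outcomes section, pre-intervention assessment on day 1 | Day 1, scan, abstinence | Day 14, scan, abstinence; day 30, no scan | Day 14 yes; day 30 not ensured |
| Outcomes section, pre-intervention assessment at Week 0 | Week 0, no scan | Day 14, scan, abstinence; day 30, no scan | Day 14 no; day 30 yes, on scan and abstinence |
| Table 1 as extracted | None shown | Day 30 | No paired test possible |

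Only the abstract dates a baseline, and it is the reading that produces the mismatch. A Week 0 baseline would remove it for day 30, but no text commits the scales to Week 0.

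**Step 2. What a shared shift does to each test.** Let τ be the true nasya effect on the change and δ the shift due to changed conditions.
- Mean change, nasya group: τ + δ. The paired test is of τ + δ = 0.
- Mean change, control group: δ.
- Difference in change: (τ + δ) − δ = τ.

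The paired test is off by δ. The between-group contrast is not.

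**Step 3. Illustration of size.** Inputs from the article: 30 per group, two-sided alpha .05. The shift δ is not in the article and is assumed.

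Paired *t* test with 29 degrees of freedom and noncentrality d × √30, where d is the shift divided by the SD of the change score, and τ = 0:

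| Assumed d | Noncentrality (d × 5.477) | Chance of P<.05 with no nasya effect |
|---|---|---|
| 0 | 0 | 5.0% |
| 0.1 | 0.548 | 8.3% |
| 0.2 | 1.095 | 18.5% |
| 0.3 | 1.643 | 35.5% |
| 0.4 | 2.191 | 56.3% |
| 0.5 | 2.739 | 75.4% |

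If the shift is instead expressed in SDs of a single score, d = shift / √(2(1 − r)), where r is the correlation between the two visits. At an assumed r = 0.5 the divisor is 1 and the table is unchanged. At r = 0.7 it is √0.6 = 0.775, and shifts of 0.1, 0.2, 0.3 and 0.5 SD give 10.5%, 27.7%, 53.6% and 92.7%.

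**Step 4. The between-group test under the same shift.** In a simulation of 20,000 trials with the same shift in both arms, the two-sample *t* test on change scores rejected in 4.8% (d = 0), 5.2% (d = 0.3) and 4.9% (d = 0.5), which is the nominal level within simulation error.

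**The case against.** The strongest reply has four parts.

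- **The timing is not settled.** The outcomes section lists an undated pre-intervention assessment. If it takes place at Week 0, baseline and day 30 are both non-scan days. This stands, and it is why the point is limited to the abstract's schedule.
- **No effect of abstinence is documented.** The article gives no size, no direction, no habitual intake and no recall period for any scale; a scale that asks about several weeks would be little touched by a 12-hour rule. Nor does it say whether the day-1 scales come before or after the scan, or what participants may drink before day 30. This also stands. The percentages above would fit any time effect of the same size and say nothing specific about caffeine.
- **The randomized comparison is already planned and is protected.** This stands too. What it does not answer is that the paired tests are planned at the same threshold, with nothing to mark them as descriptive.
- **A condensed article may leave questionnaire conditions to the full protocol.** That excuses silence about detail. It does not excuse three accounts of when the scales are taken.

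A reader might go further and infer that the nasya group's scores will improve spuriously through relief from scan-day conditions. The documents support neither the direction nor the existence of such a shift. A reader might also infer bias between groups, since on day 1 the nasya group is scanned twice and controls once and allocation is open. But the caffeine rule and scan days are common to both arms, and nothing in the article shows a differing effect on the scales.

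**Conclusion.** The point holds in a limited form. On the abstract's schedule, the within-group paired tests on the clinical scales cannot separate a nasya effect from a change in test conditions or any other effect of time. This rests on three documented facts: the restriction is tied to scans, day 30 has no scan, and the abstract dates the baseline to day 1. It also rests on one open question, because the outcomes section and Table 1 give other timing.

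The size is unknown. The range of 8% to 75% (up to 93% with a visit correlation of 0.7) shows only how sensitive a paired test with 30 participants is to assumed shifts of 0.1 to 0.5 SD; it is not an estimate for this trial. The between-group comparison is not biased by a shared shift on average. The outcomes are secondary and the article itself says the trial is not powered for clinical efficacy, so the consequence is a risk of misreading within-group results, not a flaw in the randomized comparison.

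**What to change.** 1. Reconcile the abstract, the Secondary Outcome Measures section and Table 1 into one stated timing for the scales, with the baseline visit dated.
2. Use the same test conditions, including stimulant abstinence, at every scale visit in both groups, and state whether the scales come before or after any scan that day.
3. Base conclusions on the scales on the between-group difference in change, or on a between-group comparison adjusted for the baseline score. Label the paired within-group tests as descriptive.

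The cost is small: a reminder to participants before day 30 and a few lines of text, with no new visit or instrument. Within-group P values would no longer support a conclusion of effect.

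Moving the baseline scales to Week 0 is an option, not a requirement. It would take them off a scan day, but would separate them from the baseline scan used in the planned correlations between clinical measures and imaging. Matching abstinence at day 30 deals with the caffeine difference only, since a scan-day setting at baseline would remain; the third change covers what is left.

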#### Data Collection

##### Resting Phase fMRI

In this study, a block design paradigm will be used during task phases before and after *marsha nasya karma*, where stimuli are presented continuously within specific blocks alternated with rest periods to elicit and distinguish brain responses. Resting state fMRI, on the other hand, captures spontaneous brain activity without external stimuli, allowing for the correlation of signal fluctuations among functionally related brain regions. Panbrain activation mapping will be conducted during the resting phase before and immediately after *nasya karma* therapy (within 15 min) in the trial group. fMRI will be conducted before the *nasya karma* procedure and then again after the complete procedure is over. Participants in the control group will proceed directly to fMRI. During scanning, participants will be instructed to remain still with their eyes closed for 15 minutes to avoid motion artifacts. Any head movement will necessitate repeat mapping. The resting state fMRI paradigm will map spontaneous brain activity across the visual, auditory, motor (left and right), memory, and language domains before and after *marsha nasya karma*.

##### Task-Based fMRI

###### Overview

The task paradigms in this study are designed to effectively stimulate relevant brain areas while ensuring that participant performance remains accurate. Rest blocks are strategically interspersed between active blocks to establish baseline fMRI signals and allow participants to rest. Each domain collects sufficient data through a structured design featuring at least 4 blocks per task. Task durations are optimized to maintain participant concentration without inducing fatigue; breaks are included if needed due to head movements, ensuring image consistency.

###### Visual fMRI

The study will use a checkerboard method with 8-Hz flickering alternating with 30-second rest blocks in a sequence of 1 rest cycle plus 4 flickering cycles (B, AB, ABAB, and AB). Participants receive prior education and training to understand their tasks: viewing a flickering checkerboard followed by a fixation cross during rest periods. The paradigm runs for 4 minutes and 30 seconds, minimizing eye movements while allowing for effective scene categorization.

###### Auditory fMRI

Auditory tones (1000 and 2000 Hz; ratio of 4:1) alternate with 20-second *veena* sounds in a sequence of ABABABABABAB. Participants, relaxed with their eyes closed, hear alternating tones during rest periods, with more frequent standard tones. Each auditory block is followed by a 20-second *veena* sound. The paradigm duration is 4 minutes.

###### Motor fMRI (Right and Left)

Right and left motor areas are separately mapped using hand movements. Participants perform finger movements indicated by a flashing green dot on the screen alternating with 30-second rest blocks (1 off plus 4 on cycles [BABABABAB]). They synchronize opening and closing fist movements with the dot, followed by rest periods focusing on a fixation cross. Each motor task runs for 4 minutes and 30 seconds per hand.

###### Memory fMRI

The working memory attention task lasts 6 minutes and 45 seconds, presenting numbers for 0.5 seconds with 2.5 seconds of a black screen. Blocks of 51 seconds feature numbers with 30-second rest periods in between. Participants press a button when presented with identical numbers, with task initiation and closure including 15-second rest blocks. This paradigm effectively tests working memory under fMRI conditions.

###### Principles Underlying Assessment of Brain Response to Nasya Karma

The response to *nasya karma* will be assessed considering 3 principles. The first principle is that neural activity correlates with changes in local blood oxygen levels. The second principle is that oxygenated blood exhibits different magnetic properties compared to deoxygenated blood. The third principle is that alterations in the ratio of oxygenated to deoxygenated blood, known as the hemodynamic response function, can be inferred using fMRI through the measurement of the BOLD response.

#### Blinding

In this study, participant blinding is not feasible as the intervention involves a procedural administration (*nasya karma*) where participants are aware of undergoing the procedure and the study primarily aims to evaluate the procedural effect rather than an isolated pharmacological effect. Assessor blinding will also not be implemented as the primary outcome measure is fMRI, an objective instrumental assessment that is not subject to assessor interpretation bias during data acquisition.

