### Interventions

The participants in the intervention group will be administered *nasya karma* (nasal instillation) with *anu taila* at a dose of 3 mL per nostril for 7 days (on every alternate day for 14 days) as indicated in the Ayurveda treatises for healthy individuals. Before *nasya*, local oleation and sudation of the head region will be conducted for approximately 10 minutes. Following the *nasya karma* procedure, participants will inhale medicated smoke and rinse their mouths with lukewarm water. The control group, consisting also of healthy individuals, will not undergo any interventions to facilitate assessment of the specific effects attributed to *nasya karma* in the intervention group when compared to baseline measures in healthy individuals.

*Nasya karma* will be administered by the investigator at the hospital’s *panchakarma* unit except on assessment days, when it will be conducted at AIMS. Each participant will be closely monitored for 30 minutes following the procedure to observe any immediate effects or reactions. Vital signs such as heart rate, blood pressure, and respiratory rate will be monitored and recorded before and after every session. Participants reporting any adverse symptoms experienced after each session will be recorded through a standardized format designed to capture a wide range of potential side effects, including nasal irritation, headache, dizziness, nausea, or any other discomfort. Any serious adverse event will be reported immediately to the institutional ethics committee, and a causality assessment will also be conducted. Appropriate care will be provided for all adverse events requiring medical intervention, and they will be followed up on until resolution or stabilization.

If a participant experiences significant adverse effects, such as severe nasal irritation, fever, sinusitis, or any other serious discomfort that impacts their well-being, the intervention will be immediately halted, and the participant will be withdrawn. Discontinuation will also occur in cases of noncompliance with the treatment regimen, if the participant wishes to withdraw for any reason, or if the participant meets any of the exclusion criteria during the study. As the trial involves healthy volunteers, administration of concomitant medication is prohibited during the trial period of 30 days.

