##### fMRI Data Analysis

The fMRI data will undergo preprocessing using either the Data Processing and Analysis for Brain Imaging or CONN toolboxes, which will encompass essential steps such as slice timing correction, realignment for motion correction, regression to remove confounding effects, normalization to a standard template, smoothing to enhance signal-to-noise ratio, detrending to remove low-frequency drifts, and filtering to focus on relevant frequency bands, aligning with established practices in the field. After data preprocessing, amplitude of low-frequency fluctuation, functional connectivity, and large-scale functional brain network analysis will be conducted to investigate the difference in neurophysiological responses between the groups. The results will be interpreted in the context of the experimental paradigm to elucidate neural correlates of the studied phenomena, providing insights into the effects of *nasya karma* on brain function. Voxels exhibiting expected time-course correlations (30-second periods) will receive high activation scores, whereas those showing no correlation or deactivation will receive lower or negative scores, respectively. MRI data analysis will use general linear models via statistical parametric mapping (SPM). fMRI data will be processed using MATLAB 2023 (MathWorks Inc).

Resting phase MRI data will be analyzed using software tools such as SPM, the CONN toolbox, and the Functional Magnetic Resonance Imaging of the Brain Software Library (Analysis Group), whereas task phase fMRI will specifically use SPM. Given the focus on group data in this study, complex patterns of brain activation will be interpreted collectively rather than individually. For voxel-based analysis, a significance threshold of *P*<.01 at the voxel level and *P*<.05 corrected for false discovery rate (FDR) at the cluster level will be applied. Connectome-based analysis will use a threshold of *P*<.05 corrected for FDR. Additionally, Pearson correlation analysis will be performed to explore potential associations between clinical outcomes and fMRI findings, examining changes in brain activity following different interventions.

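### The reason given for waiving assessor blinding covers only fMRI acquisition, not the anxiety and cognition ratings or image processing after the scan

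*Protocol article*

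**What the plan says.** The Blinding section first explains that participants cannot be blinded to a procedure. It then extends the waiver to assessors: "Assessor blinding will also not be implemented as the primary outcome measure is fMRI, an objective instrumental assessment", and completes the reason with "that is not subject to assessor interpretation bias during data acquisition". No other reason is offered, and no blinded rater, image reader or analyst is described anywhere in the article.

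Secondary Outcome Measures lists "anxiety assessed using the Hamilton Anxiety Rating Scale" and "cognitive function assessed via the Montreal Cognitive Assessment scale", alongside the Perceived Stress Scale and the 36-Item Short Form. It does not say who administers or scores them. Under Interventions, nasya "will be administered by the investigator". The control group receives nothing.

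fMRI Data Analysis leaves "preprocessing using either the Data Processing and Analysis for Brain Imaging or CONN toolboxes" as alternatives and adds "Resting phase MRI data will be analyzed using software tools such as SPM, the CONN toolbox" and the FSL package as examples. It fixes task-phase analysis to SPM. It sets a voxel threshold of P<.01 with cluster-level FDR at P<.05. Multiple-Comparison Correction sets an uncorrected voxel threshold of P<.001 with cluster-level FWE at P<.05, and adds FDR at the analyst's discretion.

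Data Management says the images are stored on disk and analyzed once the study is complete. Table 1 gives group A three fMRI sessions (two on day 1, one on day 14) and group B two.

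**The concern.** The waiver is wider than its justification. The scanner may well record signal without regard to the arm, but that says nothing about a person scoring an interview-based anxiety scale or a cognitive test. It also says nothing about the steps that turn recorded signal into a reported BOLD difference, such as preprocessing, motion exclusions and subject-level modelling.

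For the rated scales, a scorer who knows the arm can shift scores toward the treated group. The control arm receives nothing, so participants' own expectations may already favor nasya, and unblinded rating could add a second bias in the same direction. For the imaging, the text leaves some choices open and describes no masking while they are made. That matters because BOLD is the primary outcome and the results are meant to inform larger trials.

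**Working it through.** **Step 1: reach of the reason against reach of the waiver.**

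| Step | Does the acquisition argument apply? | What the article provides |
|---|---|---|
| Scan acquisition | Yes | Reason stated in Blinding |
| Preprocessing, motion exclusions, subject-level maps | No, these come after acquisition | No masking described; two toolboxes offered |
| Resting-state analysis | No | Open list of packages |
| Task-phase analysis | No | No masking described, but fixed to SPM |
| Thresholding | No | Two conflicting rules |
| Hamilton anxiety, Montreal cognition | No, not fMRI | No rater named, no masking |
| Perceived Stress Scale, 36-Item Short Form | No | Assumed self-reported, so assessor blinding would not protect them; left out of this point |

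**Step 2: illustrative size for the rated scales.** The article states no figure to reproduce.

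Inputs from the article: n = 30 per group (Sample Size), two-sided alpha 0.05 and an independent-samples t test (Statistical Analysis, Overview). Input assumed: a systematic rating shift of b standard deviations between arms, with a true effect of zero. The article gives no value for b, so a range is shown.

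Degrees of freedom = 2 × 30 − 2 = 58. Noncentrality = b × √(n/2) = b × √15 = b × 3.873. The false-positive rate is the probability that a noncentral t variable with these parameters exceeds the two-sided 5% critical value in either direction.

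| Assumed shift b (SD) | Noncentrality | False-positive rate |
|---|---|---|
| 0 | 0 | 5.0% |
| 0.1 | 0.387 | 6.7% |
| 0.2 | 0.775 | 11.9% |
| 0.3 | 1.162 | 20.8% |
| 0.4 | 1.549 | 33.2% |
| 0.5 | 1.936 | 47.8% |

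A middle range of 0.2 to 0.4 SD gives about 12% to 33% in place of 5%, for each affected scale taken singly.

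**Step 3: imaging.** No percentage is offered. One can compute how often at least one of several correlated tests is significant, but that describes a single scalar test at 5%. The planned inference is voxel-wise with cluster-level correction, so such a figure does not carry over.

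**Step 4: is masking practicable?** The images are stored and analyzed only after the study ends, so files can be recoded first. The one obvious giveaway is the scan count, 3 in group A against 2 in group B. A code assigned per scan, not per participant, hides it during preprocessing and subject-level work.

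**The case against.** Several objections have weight.

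- **Analysts are not mentioned.** A reader might infer that analysts will choose exclusions and models while seeing the group. The article does not say so. Its Blinding section speaks of participants and assessors and is silent on analysts, and an analysis plan that is not shown may well mask them. This stands, so the point rests on the faulty stated reason and the open or conflicting wording in the text, not on a claim about what analysts will see.
- **Pipeline choice is a matter of prespecification.** Naming one toolbox and one threshold would remove that freedom even with unblinded analysts, and the Blinding section did not create it. This is also correct. The two issues meet only because acquisition objectivity is offered as sufficient protection for a result that also depends on later choices.
- **Openness can be overstated.** A reader might take the whole imaging analysis as open. Task-phase analysis is tied to SPM. What remains open is the preprocessing toolbox, the resting-state software and the threshold rule.
- **The rater is unknown.** Scoring by a person is assumed from the usual form of these scales, and not requiring blinding does not prove that every rater will know the arm. This stands and lowers confidence.
- **The stakes are limited.** The scales are secondary, the trial is exploratory, and Strengths and Limitations says it is not powered for clinical efficacy. This limits the weight of the point but does not make the stated reason sound.

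It could also be said that the Blinding section sits under the primary outcome's methodology and so concerns fMRI alone. But Data Management and Statistical Analysis sit under the same heading and plainly apply trial-wide.

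**Conclusion.** The point holds in a limited form. The article waives assessor blinding for a reason that reaches only scan acquisition. That reason does not justify the waiver for the Hamilton anxiety and Montreal cognition ratings, nor for image processing after acquisition. This is a stated rule with an inadequate basis, not a detail left to another document.

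For the two rated scales, the illustrative size is a rise from 5% to about 12% to 33% false positives. That rests on an assumed 0.2 to 0.4 SD shift, on 30 per arm, on a true effect of zero, and on the scales being scored by someone aware of the arm. For the imaging, the concern is qualitative. The documents do not support a claim that analysts are known to be unblinded, nor an inflation percentage for the cluster-corrected analysis. They also do not support a claim that the bias can be removed entirely, since participants may tell a rater their arm. Confidence is moderate, and the point ranks as a cheap improvement.

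**What to change.** Reword the Blinding section so that the waiver applies to participants, therapists and scan acquisition only. Then add two provisions.

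1. **Images.** Store each scan under a random per-scan code that hides both the arm and the number of scans a participant had. Complete preprocessing, motion exclusions and subject-level maps in one named toolbox before the code is broken. Name the resting-state software as well. Reconcile fMRI Data Analysis with Multiple-Comparison Correction so that one threshold rule is fixed before the code is broken.
2. **Rated scales.** Where current staffing allows, have the Hamilton anxiety and Montreal cognition scales scored by existing staff at either site who did not give nasya and are not told the arm. State in the article who scores them.

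The cost is file recoding, an earlier commitment to one pipeline, and some reassignment of duties. The documents give no staffing details, so whether the second provision can be met in full is for the sponsor to judge. Rater blinding will be imperfect because participants may reveal their arm, and the report should say so.
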